**Methods:**

In this prospective multicentre cluster randomized phase-III trial patients with any incurable solid tumor and having defined cancer related symptoms, who receive new outpatient chemotherapy in palliative intention (expected tumor-size response rate ≤20%) are eligible. Immediately before the weekly visit to oncologists, all patients complete with nurse assistance the E-MO*S*AIC Assessment: Edmonton Symptom Assessment Scale, ≤3 additional symptoms, estimated nutritional intake, body weight, Karnofsky and medications for pain and cachexia. Experienced oncologists will be randomized to receive the LoMoS or not. To minimize contamination, LoMoS are removed from the medical charts after visits. Primary endpoint is the difference in global quality of life (items 29 & 30 of EORTC-QlQ-C30) between baseline and last study visit at week 6, with a 10 point between-arm difference considered to be clinically relevant. 20 clusters (=oncologists) per treatment arm with 4–8 patients each are aimed for to achieve a significance level of 5% and a power of 80% in a mixed model approach. Selected co- variables are included in the model for adjustment. Secondary endpoints include patient-perceived patient-physician communication symptom burden over time, and oncologists’ symptom management performance (predefined thresholds of symptoms compared to oncologists’ pharmacological, diagnostic or counselling actions [structured chart review]).

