### Randomization procedure and patient registration

Participating physicians are randomly allocated to the intervention or control arm. Hence, all eligible patients allocated to a physician will be under the same intervention.

Before randomization, the center needs to be activated and the initiation visit has taken place. Each physician has to be informed about the study procedures and has to sign informed consent prior to his randomization. There will be no specific training on symptom management, because the E-MOSAIC intervention in this study includes simply the monitoring sheet. Patient registration is only possible for randomized physicians. Patients give informed consent prior to any protocol-specific procedure.

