• visits (#) with shortness of breath > = 6/10 and no immediate diagnostic or therapeutic intervention

A medical fellow, having at least 2 years clinical experience, who is blinded to the randomisation (the UPI system does not allow to identify institutions nor individual oncologists), will analyse for each patient the visit description and patient recalled interventions of last visit to search for such interventions.

From the visits the following variables are collected: medications and changes, diagnostic interventions, delegated interdisciplinary interventions, and patient perceived interventions.

Additional research questions investigate factors influencing change in G-QoL, tumor response (CR, PR, SD or PD), tumor type, predominant symptom, anxiety, complexity, education and hospitalization. A predominant symptom is defined as the symptom with the highest ranking and all other symptoms are > =2 / 10 lower ranked. Complexity is defined as > =3 symptoms with > =6/10, with the exception of fatigue and anorexia (threshold > =9/10).

To explore patients’ subjective adaptation to illness and burden of treatment two linear analogue self-assessment (LASA) indicators are included, assessing perceived adjustment to chronic illness (PACIS); [34] (‘no effort at all’ – ‘a great deal of effort) and overall treatment burden (‘not at all’ – ’severely’). The indicator for PACIS was confirmed to be responsive to cytotoxic side-effects, mental distress, and psychosocial dysfunction in patients with early breast cancer [36]. It is suitable to describe patients’ adaptation over time. The instruments are validated [37]. The indicator for overall treatment burden has been validated regarding side-effects of antiemetic and cytotoxic therapy [38].

As indicator for decision-making preferences, the difference in number of mismatched decision-making preferences between week 3 and 6 will be compared between the two arms.

Patients’ preferences for involvement in decision making will be assessed by a measure adapted from previous studies [39]. The patient chooses from among five categories ranging from ‘the doctor should make the decision using all that he/she knows about the treatment’ to ‘I should make the decision using all that I know and learn about the treatment’. In addition the physician is asked to choose from among the same five categories how he/she estimates the patients’ preferences.

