### Data analysis

Due to the cluster structure, comparisons of different outcomes between treatment arms will be analyzed by mixed models. For endpoints with continuous values, linear mixed model may be applied. For endpoints with categorical or binary values, nonlinear mixed model or generalized estimating equations may be applied.

The data will be stored and analyzed at the SAKK Coordinating Center using SAS software, Version 9.2 of the SAS System for Windows (SAS Institute Inc., Cary, NC, USA) and the open source R statistical software package (http://www.r-project.org/). All statistical tests will be done two-sided at a significance level of 0.05. P-values will be corrected for multiple testing where appropriate.

Descriptive statistics will be done by median and range for continuous variables. Categorical data will be reported using absolute and relative frequencies.

For the *primary endpoint*, selected influential variables (education, tumor type, predominant symptom, anxiety, complexity, hospitalisations) and the baseline G-QoL value will be included in the analysis model as covariates. For the primary analysis, only evaluable patients will be used. As a sensitivity analysis, non-evaluable patients will be included if possible. For instance, the difference between baseline and 3 weeks will be analyzed including patients who are evaluable at week 3 but non-evaluable at week 6.

Several pre-defined subgroup analyses are foreseen: The difference in G-QoL will be compared between both arms in sub-groups of patients having

a) a tumor size response (SD, PR, CR) or not (PD),

b) basic education or additional education

c) one of the main tumor types defined as composing > = 20% of the evaluable study patients.

d) a predominant symptom, if composing > = 20% of the evaluable study patients (expected based on symptom epidemiology data: pain, anorexia and/or fatigue [both predominant vs. other symptoms or alone vs. other symptoms], anxiety and/or depression [both predominant vs. other symptoms or alone vs. other symptoms], nausea, shortness of breath).

e) anxiety <6/10 or > =6/10

f) complexity less than 3 symptoms above threshold vs. > = 3 symptoms above threshold (fatigue and anorexia > =9/10, other symptoms > =6/10).

All subgroup analyses will include baseline G-QoL as covariate.

The study population will be described separately by institution (study center)-, oncologist-, and patient-related factors.

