### Strengths

The strength of our approach, is the defined clinical setting, chemotherapy in palliative intention, where disease related symptoms, treatment related toxicities and clinical benefit parameters guide treatment.

In contrast to the previous studies which aimed at a general improvement of communication our study aims to improve symptom control due to more in depth symptom assessment and adaption of chemotherapy due to better monitoring of toxicity and clinical benefit parameters.

A second strength is the multicenter setting which tests the intervention in a real life environment and differences between centers can be further studied.

The main focus on specific and generic patient reported outcomes (quality of life, and symptoms) reflects patient centered care in the oncological setting.

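### The planned comparison of arms within tumor-response subgroups conditions on a post-randomisation variable that the intervention may affect, so subgroup (a) should be descriptive only

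*Protocol article*

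**What the plan says.** All references are to the protocol article.

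- **Data analysis** introduces the subgroups with "Several pre-defined subgroup analyses are foreseen" and describes the analysis as "The difference in G-QoL will be compared between both arms in sub-groups of patients having" each listed feature. Item (a) is "a tumor size response (SD, PR, CR) or not (PD"). Items (b) to (f) are education, main tumor types, predominant symptom, anxiety and complexity. Baseline G-QoL is a covariate in every subgroup analysis. The same section states: "P-values will be corrected for multiple testing where appropriate".
- **Objectives and endpoints** lists "tumor response (CR, PR, SD or PD") among the factors whose influence on G-QoL change is an additional research question. It gives no assessment time.
- **Abstract, Methods** describes the patients as those "who receive new outpatient chemotherapy in palliative intention".
- **Randomization procedure and patient registration** states: "Patient registration is only possible for randomized physicians".
- **Strengths** names as an aim of the study, besides better symptom control, the "adaption of chemotherapy due to better monitoring of toxicity and clinical benefit parameters".

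**The concern.** A subgroup comparison keeps the protection of randomisation only if the grouping variable cannot be changed by the allocated arm. Tumor response to chemotherapy started at study entry does not meet that condition. It arises while the patient is under the care of a physician who does or does not receive the monitoring sheet, and the article itself names a route by which the sheet could alter chemotherapy.

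Suppose the intervention moves some patients from progression to non-progression. Those patients will tend to have a worse prognosis than the ones who would not have progressed anyway, and a better prognosis than the ones who progress regardless. Both response groups in the intervention arm then hold a poorer mix than their counterparts in the control arm. A difference in G-QoL change can appear in each group although the intervention does nothing to G-QoL. If the intervention lowered the response rate, the sign would reverse. At stake is a non-randomised contrast that would be reported with the standing of a pre-defined trial comparison.

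A smaller point concerns the whole list. Comparing the arms inside each subgroup does not by itself test whether the effect differs between subgroups, which is the question that subgroup analyses are usually read as answering.

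**Working it through.** **1. The design figures, to fix the scale.** Inputs from Sample size calculation: variance 400 (SD 20), ICC 0.05, difference 10, two-sided alpha 0.05, power 0.8, 12 physicians per arm with 8 patients each. For k clusters of m patients per arm, SE = sqrt(2 × 400 × (1 + (m − 1) × 0.05) / (k × m)).

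- 12 × 8 per arm: SE = sqrt(800 × 1.35 / 96) = 3.35. Power from the noncentral t with 22 df is 0.813. Eleven clusters give 0.775, so the stated 192 patients reproduce.
- Revised plan in the Interim analysis section, 20 × 4 per arm (160 patients): power is 0.820 by the same method.

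Neither figure involves tumor response. Tumor response is also not among the covariates listed for the primary model.

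**2. Order of events.** The physician is randomised, the patient is registered, new chemotherapy starts, and response is observed. No reading of item (a) makes it a baseline variable.

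**3. How large the bias could be.** The documents give no figures for this, so the inputs are assumptions: SD of G-QoL change 20, a prognostic factor correlated 0.7 with latent response and 0.5 with G-QoL change, and no arm effect on G-QoL. Response means that the latent score exceeds zero, and the arms are shifted by +b/2 and −b/2. Within responders, the spurious difference (intervention minus control) is

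20 × 0.5 × 0.7 × [φ(b/2)/Φ(b/2) − φ(b/2)/Φ(−b/2)].

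By symmetry the same expression holds among non-responders.

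| Response, control vs intervention | Calculation | Spurious difference | Simulation (2,000,000 patients): response group, PD group |
|---|---|---|---|
| 50% vs 50% (b = 0) | 7 × 0 | 0 | 0.08, 0.01 |
| 45% vs 55% (b = 0.25) | 7 × (0.720 − 0.879) | −1.1 | −1.04, −1.12 |
| 40% vs 60% (b = 0.5) | 7 × (0.646 − 0.964) | −2.2 | −2.16, −2.23 |

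The difference over all simulated patients was 0.04, so the bias comes from the conditioning and not from the data. Adjustment for baseline G-QoL was not modelled. It could remove part of the bias, to the extent that baseline G-QoL carries the shared prognosis.

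**4. What comparisons inside subgroups can show.** Take 160 evaluable patients (20 clusters of 4 per arm), ICC 0.05, SD 20, the normal approximation, and a true effect of 10 points that is the same in everyone. Treat the two subgroups as independent.

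- 50:50 split, 40 per arm and 2 per cluster in each subgroup: SE = sqrt(800 × 1.05 / 40) = 4.58, and power = Φ(10/4.58 − 1.96) = 0.59. The chance that exactly one subgroup is significant is 2 × 0.588 × 0.412 = 0.48.
- Interaction at 50:50: SE = sqrt(21 + 21) = 6.48. Power for a 10-point difference in effect is Φ(10/6.48 − 1.96) = 0.34.

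| Split | Power in each subgroup | Exactly one significant | Interaction power, 10-point difference |
|---|---|---|---|
| 50:50 | 0.59, 0.59 | 0.48 | 0.34 |
| 30:70 | 0.41, 0.72 | 0.54 | 0.30 |
| 20:80 | 0.29, 0.77 | 0.61 | 0.24 |

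A uniform effect would therefore look like effect modification about half the time, if significance in one subgroup and not the other were taken as evidence of it.

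**The case against.** The bias in (a) is conditional. It needs the intervention to change response status, and the article states an aim for chemotherapy adaptation, not an expected effect on tumor size. The trial lasts 6 weeks, expected tumor response is at most 20%, and the intervention is the sheet alone, without training in symptom management. A large shift in response between arms is not the obvious expectation. Even a shift of 20 percentage points gives only about 2 points under the assumptions tried. This stands, and it limits the size of the concern. It does not remove the concern, because the trial cannot establish in advance that response is unaffected.

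Some stronger readings are tempting but not supported:

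- A reader might infer that all the subgroup analyses are biased in this way. Education and tumor type are not on-study outcomes. For predominant symptom, anxiety and complexity, Data analysis gives no time point, and nothing shows that post-baseline values are meant.
- A reader might infer that interaction tests have been ruled out. The wording describes arm comparisons in subgroups and mentions no interaction, but it excludes none, and the analysis plan is not shown.
- A reader might infer that error inflation across many subgroups is uncontrolled. The article promises correction where appropriate, although it names no method or family. The number of subgroups under (c) and (d) depends on the observed data, and the subgroups overlap, so no overall error rate can be derived.
- A reader might infer that a difference seen only in responders would be selection alone. At the 10-point size the trial seeks, the illustrations do not support that.

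Counting stable disease with response is a definitional choice that the article states openly, so it is not part of this point.

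**Conclusion.** The concern holds for subgroup (a). The article fixes both the grouping variable and the arm comparison. The variable is observed after randomisation, and the article supplies a path from the intervention to it. The contrast is therefore not a protected randomised comparison, and an interaction test would not repair it, because the grouping itself is at fault.

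The likely size is modest: about zero if response does not depend on arm, and about 1 to 2 points for a difference in response of 10 to 20 percentage points. These figures rest on assumed correlations of 0.7 and 0.5 and an SD of 20. Stronger shared prognosis or a larger shift in response would raise them, and weaker would lower them. The primary analysis and the sample size are unaffected.

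For (b) to (f) the point is an improvement and not a bias. The comparison as stated does not test whether effects differ, and an explicit interaction estimate would.

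**What to change.** 1. Take (a) out of the arm-by-subgroup comparisons, or keep it with an explicit label as non-randomised and descriptive. Report tumor response by arm, and report the association of response with G-QoL change. The latter is already among the additional research questions.
2. For (b) to (f), state that the grouping uses baseline values. Estimate one arm-by-subgroup interaction per factor in the mixed model on all evaluable patients. Report within-subgroup estimates with confidence intervals, labelled exploratory.

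The cost is a change of analysis wording, with no new data and no change in sample size. One planned subgroup comparison is lost. The interaction tests will have low power, about 24 to 34% for a 10-point difference in effect under the assumptions above, so a non-significant interaction must not be read as showing that the effect is uniform.

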### Ethical considerations

This protocol was written, and the study is to be performed in accordance with the Declaration of Helsinki and the Guidelines of Good Clinical Practice issued by ICH. The study has been approved by the local ethics committees of the cantons of all participating centers (Aarau, Basel, Bern, Zuerich, Fribourg, Graubuenden, St.Gallen, Ticino). There is no approval outstanding.

All patients are informed of the aims and procedures of the study. They are informed as to the strict confidentiality of their data, but they need to know that their medical records may be reviewed for study purposes by authorized individuals other than their treating physician.

Informed consent is obtained on a written form approved by the local ethics committee. Two copies of the informed consent have to be signed, one of which is handed to the patient.

Patients have the right to refuse further investigations for any reason and at any time. Patients who decide to withdraw from the study should be asked whether they also want to withdraw their consent for their data to be used for the follow-up assessments. It is emphasized that participation is voluntary and that the physician is allowed to refuse further participation in the study whenever he/she wants. Physician’s informed consent is obtained on a written form.

## Discussion

This study evaluates the effects of longitudinal assessment of symptoms and syndromes in patients receiving anticancer treatment for advanced cancer in palliative intention on health related quality of life, symptoms, communication and physicians performance.

### Interim analysis

The interim analysis was based on the data from 89 patients coming from 31 different physicians. Of those, the data from 8 patients could not be used, since they were assigned to physicians who enrolled only one patient, i.e. they cannot be used to estimate within cluster correlation. At that time already 160 patients allocated to 47 physicians had been accrued. Unexpectedly a negative ICC was found. A literature search on negative ICCs only revealed that this appears in case of very similar but rather small clusters [42]. This translates to a negligible between-cluster variation and a dominant within-cluster variation which in turn is the case for very small ICCs. Then a simulation study using the design parameters of this trial and a SAS macro for power calculations (fpower.sas) was performed [43]. It seemed that an increasingly negative ICC does not diminish the power, but rather that the power increases further. Hence the sample size was not adapted for this reason.

However, during the interim analysis three problems arose regarding the sample size:

a) None of the predefined scenarios met the reality of cluster sizes accumulated in the first three years: instead, the vast majority of clusters were smaller than expected.

b) An unexpectedly high number of patients were not evaluable for primary endpoint according to the requirements specified in and implied by the protocol. Although the original protocol focused on evaluable patients, it did not foresee additional patients to be accrued to account for non-evaluable patients.

c) There were many clusters with only one or two or even no patients. These are problematic because they do not allow to properly calculating the within-cluster correlation required for the interim and final analysis. In fact, this renders patients who are evaluable of limited value for the analysis. While the trial design allows for varying and even small cluster sizes it is not clear how these very small clusters will affect the final results. Moreover, while there are approximate formulae to adjust the final sample size for varying cluster sizes, these only apply to approximate calculations which were not used during the trial development. These problems revealed from the interim analysis led to the following conclusions which were documented in a note to file:

1) 160 patients will be required, distributed to four patients per cluster with twenty clusters per treatment arm.

2) An additional five per cent, i.e. eight patients, will be accrued to account for varying cluster sizes.

3) That is, in total 168 evaluable patients will be accrued to meet the design specifications of the protocol (alpha = 5%, power = 80%).

Because of the problems described in b) and c) even 240 accrued patients (the maximum foreseen in the protocol although there only evaluable patients were mentioned) would not have been sufficient to obtain 168 evaluable patients. Hence, it was decided by the trial team members at the SAKK CC on April 20, 2011 to accrue an additional 10 percent, i.e. 24 patients, resulting in a total of 264 patients.

### Context

Several studies assessed whether the provision of HRQL data to oncologists, using touch pad symptom assessment devices, [24,44] by using prompt sheets [45,46] or summaries of HRQL, [47] improve communication between oncologist and patient and symptom control. The provision of a summary of HRQL (EORTC-QLQ-C30) to patients and oncologists in a randomized crossover trial resulted in more frequent discussion of HRQL issues and detection of unexpected psychosocial topics and symptoms [14].

Longitudinal symptom assessment by means of computers is feasible in the multicenter setting even for a long time span. In a recently published study patients were invited to report symptoms (Common Terminology Criteria for Adverse Events CTCAE) on an online platform. Of 125 invited, 105 participated for the mean length of one year and showed a high compliance and high satisfaction with the system, however there was only a marginal effect on communication [11].

Randomized controlled trials focused mainly on improvement of communication and symptom distress. A palm based interactive tailored patient assessment, containing a selection of symptoms, problems and concerns, rating of this items from 1–4 and prioritization for support was tested in 145 lymphoma and leukemia patients in a single centre in Norway. The assessment output was immediately delivered to treating physicians and nurses in the intervention group. The outcomes measured were the same assessments: Numbers of symptom problems and concerns addressed, change in symptom distress and need for support. In the intervention group there were more symptoms addressed, less symptom distress measured and patient were less in need for symptom management support [48].

A second randomized controlled trial investigated the effect of the ESRA-C (electronic self-report assessment cancer) on in 660 cancer patients at two institutions. The output from the ESRA-C was displayed to the treatment team in the intervention group. The primary outcome was the likelihood of discussion of symptoms and quality of life issues (SQLIs) between clinicians and patients and the secondary endpoints the visit duration and the perceived usefulness by clinicians. When the SQLIs were considered as problematic, they were more frequently discussed during the visit in the intervention group; the length of visit time was equal between the two groups. The clinicians perceived the output as useful [20].

